## Abstract

**Background:**

Smoking is the leading cause of preventable morbidity and mortality in the United States. Individuals with low socioeconomic status have disproportionately high smoking rates and greater difficulty quitting smoking. Efficiently connecting underserved smokers to effective tobacco cessation programs is crucial for disease prevention and the elimination of health disparities. Smartphone-based interventions have the potential to enhance the reach and efficacy of smoking cessation treatments targeting underserved smokers, but there is little efficacy data for these interventions. In this study, we will partner with a large, local hunger-relief organization to evaluate the efficacy and economic impact of a theoretically-based, fully-automated, and interactive smartphone-based smoking cessation intervention.

**Methods:**

This study will consist of a 2-group randomized controlled trial. Participants (*N* = 500) will be recruited from a network of food distribution centers in West Central Florida and randomized to receive either Standard Treatment (ST, *n* = 250) or Automated Treatment (AT, *n* = 250). ST participants will be connected to the Florida Quitline for telephone-based treatment and will receive a 10-week supply of nicotine replacement therapy (NRT; transdermal patches and lozenges). AT participants will receive 10 weeks of NRT and a fully-automated smartphone-based intervention consisting of interactive messaging, images, and audiovisual clips. The AT intervention period will span 26 weeks, with 12 weeks of proactive content and 26 weeks of on-demand access. ST and AT participants will complete weekly 4-item assessments for 26 weeks and 3-, 6-, and 12-month follow-up assessments. Our primary aim is to evaluate the efficacy of AT in facilitating smoking abstinence. As secondary aims, we will explore potential mediators and conduct economic evaluations to assess the cost and/or cost-effectiveness of ST vs. AT.

**Discussion:**

The overall goal of this project is to determine if AT is better at facilitating long-term smoking abstinence than ST, the more resource-intensive approach. If efficacy is established, the AT approach will be relatively easy to disseminate and for community-based organizations to scale and implement, thus helping to reduce tobacco-related health disparities.

**Trial registration:**

Clinical Trials Registry NCT05004662. Registered August 13, 2021.

## Background

In the United States (US), smoking is the leading cause of preventable morbidity and mortality [1]. Although overall smoking rates have declined in recent years, smoking is most concentrated among adults with the lowest levels of education, income, and occupational status—or those with low socioeconomic status (SES; [2]). Low-SES smokers are just as likely as those with higher SES to make a quit attempt [1], but they have greater difficulty quitting and remaining abstinent [3]. This is at least partially because low-SES smokers have less access to evidence-based and effective smoking cessation resources and are less likely to use such resources [4]. Thus, cigarette smoking accounts for a significant proportion of socioeconomic disparities in the incidence and mortality of disease [1, 5, 6]. Efforts are needed to connect low-SES smokers with effective, accessible, and engaging smoking cessation treatments to prevent disease and eliminate tobacco-related health disparities.

### Quitline-delivered smoking cessation treatment

Our team has developed partnerships with several safety-net hospitals and HIV clinics to identify and connect underserved smokers with evidence-based smoking cessation treatment delivered via state quitlines [7–10]. We developed Ask Advise Connect (AAC) to help link smokers with treatment via an automated connection system within the electronic health record. AAC has demonstrated tremendous potential as an efficient means for helping smokers obtain evidence-based treatment [7–10]; however, interventions such as AAC that depend on connecting smokers in healthcare settings with quitlines may not be adequate for low SES smokers. National data indicate that smokers and individuals with low SES do not regularly visit healthcare providers [3, 11, 12], and when they do, they are not regularly asked about their smoking status, advised to quit smoking, or offered help with quitting [13]. Moreover, in recent years, many state quitlines have experienced budget cuts, forcing them to limit or suspend services [14–16]. Phone-based counseling also has limited appeal, as quitlines reach only 1–2% of smokers [17]. In order to adequately reach underserved smokers, efforts are needed to develop and improve access to evidence-based treatments that can be delivered in the community.

### Mobile technology and smoking cessation treatment

In the US, smartphone ownership is widespread. In April 2021, the Pew Research Center reported that 85% of US adults own a smartphone [18]. Smartphone ownership is high among individuals between the ages of 18–64 years (83%) and racial/ethnic minorities (83%). It is also high among individuals with less than a high school education (75%) and an annual household income of less than $30,000 (76%) as well as those living in rural communities (80%). Additionally, the Pew Research Center reported that many US adults depend on their smartphones for all internet access. This proportion is high among racial/ethnic minority groups (vs. whites), individuals with lower education and income, and those living in rural communities. These trends suggest that smartphone-delivered interventions might be an excellent method for reaching smokers from underserved populations (e.g., low SES, rural, racial/ethnic minority).

Prior studies have used cell phones to administer text message-based, or short message service (SMS), smoking cessation interventions. Results suggest that these interventions are efficacious [19–21] and cost-effective [22, 23]. In fact, text message-based smoking cessation interventions are one of the most affordable interventions for global tobacco control [24], and these interventions have been endorsed by various organizations, including the World Health Organization [25, 26]. Smartphones have greater capability than cell phones and can be used to access the internet, run applications (apps), view and send graphic messages, and stream audiovisual content. Smartphone-delivered interventions, using mobile websites and apps, have been developed; yet many of these treatments do not adhere to the evidence-based practices established by the Treating Tobacco Use and Dependence Clinical Practice Guideline, and there is surprisingly little efficacy data for these interventions [27, 28]. Such evidence is particularly lacking among low-SES smokers [29]. Given the ubiquity of smartphones, interventions utilizing smartphones have the potential to enhance the reach and efficacy of smoking cessation interventions targeting underserved smokers.

### Objectives

This paper describes the protocol for a randomized controlled trial (RCT) that will evaluate the efficacy and economic impact of a theoretically-based, fully-automated smartphone intervention targeting underserved smokers recruited through a large, local hunger-relief organization in West Central Florida. Participants (*N* = 500) will be randomized to 1 of 2 treatment conditions: 1) Standard Treatment (ST; *n* = 250) or 2) Automated Treatment (AT; *n* = 250). ST participants will be electronically connected to the Florida Quitline (Tobacco Free Florida). This approach is designed to mirror AAC, which was developed by our team to link smokers in healthcare settings with quitline-delivered treatment. ST will be compared to AT, a fully-automated treatment enrollment and delivery approach. AT participants will receive an interactive smartphone-based intervention including individually-tailored audiovisual and text content. Combination nicotine replacement therapy (NRT) in the form of transdermal patches and nicotine lozenges will be provided to all participants.

The primary aim is to evaluate the efficacy of AT in facilitating smoking abstinence. We hypothesize that at the 12-month follow-up assessment, self-reported smoking abstinence rates will be higher in the AT group (vs. ST). Secondary aims are to: 1) compare the magnitude of the mediated effects via common mechanisms (i.e., motivation, agency, stress/negative affect) on smoking abstinence between the ST and AT treatment groups and 2) conduct economic evaluations to evaluate the cost and/or cost-effectiveness of ST vs. AT.

Through these aims, we will determine if AT performs better—in terms of facilitating long-term smoking abstinence—than the ST approach. If efficacy is established, the AT approach will be scalable and easily implemented by community-based organizations.

## Methods

### Design overview

This study will utilize a 2-group RCT to compare the efficacy of ST vs. AT among 500 participants (250 per group). We will enroll up to an additional 20 participants (up to 10 per group) as part of a 12-week pilot study that will be conducted prior to the full trial.

Participants will be current smokers recruited from a network of food distribution centers in West Central Florida. Participants will complete screening, baseline, and 3-, 6-, and 12-month follow-up assessments in person, over the phone, or online using the Research Electronic Data Capture (REDCap) platform [30, 31]. Brief 4-item weekly smartphone assessments will be administered throughout treatment. Please refer to Fig. 1.

**Fig. 1 Fig1:**
[figure not shown]
CONSORT diagram depicting trial design

### Eligibility criteria

Inclusion criteria are: 1) at least 18 years of age; 2) English or Spanish speaking; 3) smoked at least 100 cigarettes in lifetime; 4) currently smoke at least 5 cigarettes a day; 5) willing to make a quit attempt within 1 week of enrollment; 6) possess a smartphone with a data plan and operating system compatible with the project app; and 7) have a valid email address. Exclusion criteria include the following: 1) medical condition that precludes the use of NRT; 2) current use of smoking cessation medications; 3) enrolled in another smoking cessation study; 4) household member enrolled in the study; 5) inadequate health literacy; and 6) failure to electronically confirm participation within 14 days of randomization via an electronic link.

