### Randomization

Following completion of the baseline assessment, participants will be randomized to treatment group (ST or AT) using stratified randomization. Sex assigned at birth and nicotine dependence, as measured with the Heaviness of Smoking Index (HSI), will serve as the stratification variables.

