#### Primary aim

Our overarching aim is to evaluate the efficacy of AT on facilitating smoking abstinence. The primary outcome is self-reported 7-day point prevalence abstinence at the 12-month follow-up. We hypothesize that smoking abstinence rates will be higher in the AT (vs. ST) group. Using intention-to-treat methodology, we will code participants who do not complete follow-up as smoking. We will test this hypothesis using log-binomial regression, with intervention group as the primary predictor. We will control for relevant covariates (e.g., baseline nicotine dependence) and examine if treatment effects differ by sex assigned at birth.

Comparable analyses will evaluate the interventions’ effects on other definitions of smoking abstinence, including biochemically-verified abstinence using salivary cotinine and self-reported 24-h, 30-day, and continuous abstinence. We will also use smoking status at 3- and 6-months to evaluate the efficacy of AT. Generalized linear mixed models (GLMMs) with a log link function and the appropriate random-effect covariance structure will be used to analyze these data. Intervention, time, and their interaction will be included and tested in the model.

#### Secondary aim 1

We will evaluate the magnitude of the mediated effects via common mechanisms (i.e., motivation, agency, stress/negative affect) on smoking abstinence. Although we hypothesize common mechanisms of AT and ST, it will be important to pinpoint the relative strengths and weaknesses of the mechanisms in facilitating abstinence. These hypotheses can be tested using mediation analyses with intervention group (ST vs. AT) as the independent variable, abstinence at 12 months as the outcome variable, and the hypothesized mechanisms (motivation, agency, stress/negative affect) as potential mediators. To test these hypotheses, we will fit single and multiple mediator models, using the approaches of MacKinnon and colleagues [96] and Preacher and Hayes [97–99].

#### Secondary aim 2

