#### Missing data and dropouts

Participants who do not complete follow-up will be coded as smokers. It should be noted that there are problems with this approach, particularly when comparing interventions with differential dropout rates [112]. Therefore, we will manage missing smoking status data using multiple imputation under the missing-at-random (MAR) assumption. We will also conduct pattern-mixture and selection models under the missing-not-at-random (MNAR) assumption [113].

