#### Power considerations

Participants who do not complete follow-up will be classified as smokers for the primary analysis. We estimated power for self-reported abstinence between treatment groups at the 12-month assessment [114]. Based on findings from our AAC implementation study [9, 10], we expect an abstinence rate of 5% in ST. With 250 participants per group, a 2-group large-sample normal approximation test of proportions with a 2-sided 0.05 significance level will have 80% power to detect an increase in abstinence of 7% in AT vs. ST.

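### Exclusion criterion 6 is applied after randomization and conflicts with the intention-to-treat primary analysis

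*Protocol article*

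**What the plan says.** Three parts of the protocol article bear on this.

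- **Timing of allocation (Randomization).** "Following completion of the baseline assessment, participants will be randomized to treatment group (ST or AT) using stratified randomization".
- **Exclusion (Eligibility criteria, item 6).** "failure to electronically confirm participation within 14 days of randomization via an electronic link".
- **Primary analysis (Data analysis plan, Primary aim).** "Using intention-to-treat methodology, we will code participants who do not complete follow-up as smoking". The power section repeats the rule: "Participants who do not complete follow-up will be classified as smokers for the primary analysis". The section on missing data and dropouts codes non-completers the same way, while conceding that "there are problems with this approach, particularly when comparing interventions with differential dropout rates". It adds multiple imputation and missing-not-at-random models.

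The text shown does not say whether non-confirmers stay in the analysis, whether they are replaced, whether participants know their arm when they confirm, or whether the 500 are counted at randomization or at confirmation.

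**The concern.** The criterion is a behaviour observed after allocation, not a baseline characteristic. A randomized participant who fails it meets an exclusion criterion. Applied as written, the compared groups are those who confirmed, not those who were randomized.

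This collides with the plan's own handling of disengagement. Two people in the same arm may both drop out early. The one who never confirms by day 14 is excluded. The one who confirms and then stops responding is retained and counted as a smoker. The planned remedies for dropout (coding as smoking, imputation, missing-not-at-random models) cannot reach people who are excluded before they apply.

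At stake is the balance that randomization provides. If confirming depends on the arm, the 12-month risk ratio can be shifted in either direction, and the data needed to repair it may not have been collected.

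**Working it through.** **1. The plan's own power figure.** Inputs from Power considerations: "we expect an abstinence rate of 5% in ST"; "80% power to detect an increase in abstinence of 7% in AT vs. ST", read as an absolute increase, so AT = 12%; "2-sided 0.05 significance level"; 250 per group.

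- Pooled rate = (0.05 + 0.12)/2 = 0.085.
- SE under the null = √(0.085 × 0.915 × 2/250) = 0.02494.
- SE under the alternative = √(0.05 × 0.95/250 + 0.12 × 0.88/250) = 0.02475.
- Power = Φ[(0.07 − 1.96 × 0.02494)/0.02475] = 80.3%.

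The stated 80% reproduces and is not in dispute.

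**2. Order of events.** Baseline, then randomization, then up to 14 days for confirmation. Criterion 6 therefore cannot be assessed before allocation.

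**3. What exclusion does to the risk ratio.** The document gives no non-confirmation rate, so these inputs are assumptions: no true effect; the same abstinence p in both arms among all randomized; every non-confirmer smokes; 250 randomized per arm; fractions f(ST) and f(AT) excluded.

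- Abstinence among those analysed = p/(1 − f).
- Analysed risk ratio (AT/ST) = [1 − f(ST)]/[1 − f(AT)]; p cancels.

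The type I error is that of the two-sided 0.05 test in step 1, with 250 × (1 − f) analysed in each arm.

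| Excluded ST / AT | Risk ratio | Type I error, p = 5% | Type I error, p = 12% |
|---|---|---|---|
| 10% / 10% | 0.90/0.90 = 1.00 | 5.0% | 5.0% |
| 10% / 20% | 0.90/0.80 = 1.125 | 6.1% | 7.9% |
| 20% / 10% | 0.80/0.90 = 0.89 | 6.1% | 7.9% |
| 10% / 30% | 0.90/0.70 = 1.29 | 10.3% | 18.8% |

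For example, at p = 5% with 10% / 20% excluded, ST = 0.05/0.90 = 5.56% and AT = 0.05/0.80 = 6.25%.

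Keeping all randomized participants, with non-confirmers coded as smoking, gives p in both arms and a risk ratio of 1.00 in every row.

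**4. Power with and without exclusion.** Suppose 500 are randomized and a fraction f of each arm does not confirm. Two readings of 5% and 12% are possible.

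| f | Rates hold for all randomized: exclude (keep) | Rates hold for confirmers: exclude (keep) |
|---|---|---|
| 10% | 80.7% (80.3%) | 76.1% (75.6%) |
| 15% | 81.0% (80.3%) | 73.6% (73.0%) |
| 20% | 81.3% (80.3%) | 71.0% (70.2%) |

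Under the first reading, exclusion raises the rates to 5%/(1 − f) and 12%/(1 − f) with 250 × (1 − f) per arm. Under the second, keeping everyone lowers them to 5% × (1 − f) and 12% × (1 − f) with 250 per arm. In both readings, exclusion has slightly more power than keeping everyone.

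**The case against.** The strongest reply is that removal from the analysis is inferred. No sentence says non-confirmers leave the analysis set, and the rule that codes non-completers as smoking, read literally, covers a randomized person who never confirms. The article's trial-flow figure and schedule table are not shown, and the full protocol or SAP may settle the matter. This stands as a limit on what can be asserted. It does not dissolve the conflict: the article states both a post-randomization exclusion and intention-to-treat. If non-confirmers are in fact retained, criterion 6 is wrongly listed as an exclusion and still needs correcting.

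Second, arm-dependent confirmation is not documented. The article describes a single link, and every participant must have a compatible smartphone and an email address. The contrast between the app (AT) and an emailed or texted link (ST) is described for the weekly assessments, not for the confirmation link. A reader might infer that participants confirm knowing their arm; the text does not say so. It also describes no concealment until confirmation, so differential confirmation remains possible but unproven.

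Third, a reader might infer that exclusion costs power, for example a fall from 80% to 76%, 74% or 71% when 10%, 15% or 20% are excluded. Those values arise only if 500 are randomized and 5% and 12% describe confirmers. Retaining everyone under that same reading gives no more power, so the loss is not an argument against exclusion.

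**Conclusion.** The contradiction is established by the text: an exclusion assessed after randomization does not fit an intention-to-treat analysis that counts non-completers as smokers. The passages must be reconciled.

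The consequence is conditional. If non-confirmation differs by arm, the risk ratio can be biased towards or against AT; the illustrative values of 1.125 and 0.89 rest wholly on assumed exclusion rates, no true effect and all non-confirmers smoking. If non-confirmation is alike across arms in frequency and in the kind of participant, there is no bias under the null; what changes is the population described, with higher abstinence in both arms. The documents do not support a claim that bias will occur, that it favours AT, or that exclusion lowers power relative to keeping everyone.

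**What to change.** - **Preferred:** complete the electronic confirmation between baseline and randomization, so that only confirmed participants are allocated.
- **If enrolment has begun:** delete criterion 6 as an exclusion and state that every randomized participant stays in the primary analysis, coded as smoking if 12-month status is missing.
- **In either case:** state that N = 500 counts randomized participants. Report non-confirmation by arm in the participant flow; under the first option it arises before allocation and is reported as a single pre-randomization count.

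The cost is a short amendment with a changed step order, or a sentence or two on the analysis set. Under the second option abstinence rates may be slightly lower. So may power, if 5% and 12% were meant for confirmed participants (75.6% with an assumed 10% non-confirming, 70.2% with 20%). The sponsor should therefore say which population those rates describe.

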### Recruitment and screening

We have developed a partnership with a large, local hunger-relief organization that is part of the national Feeding America network. Annually, this organization provides more than 95 million meals to nearly 1 million food insecure families in the 10-county area of West Central Florida. Study staff will recruit participants from affiliated food distribution centers using face-to-face, online, and remote (e.g., flyers, staff referrals) recruitment methods. Cigarette smoking prevalence in the general population is 13.7% [32], yet smoking rates are higher among individuals with low SES and the food insecure [2, 33]. Given the broad reach of this hunger-relief organization, we believe that our recruitment goal of 500 participants is attainable.

Study staff screen potential participants for eligibility in person, over the phone, or online. Eligible individuals who are interested in participating will provide informed consent in person, over the phone, or online, and they will receive a copy of the informed consent document. They will then complete a baseline assessment in REDCap. See Table 1 for a full list of measures.

**Table 1 Tab1:**
[figure not shown]
SPIRIT Flow Diagram of enrollment, interventions, and assessments

* Denotes brief version (brief 1-item versions as adapted from the full scales) [34–57]

### Randomization

Following completion of the baseline assessment, participants will be randomized to treatment group (ST or AT) using stratified randomization. Sex assigned at birth and nicotine dependence, as measured with the Heaviness of Smoking Index (HSI), will serve as the stratification variables.

### Participant tracking, compensation, and retention procedures

We will use several approaches to maximize follow-up. Baseline and the 3-, 6-, and 12-month assessments will be conducted in person, over the phone, or online at participants’ convenience via REDCap. In-person assessments will be scheduled to coincide with participants’ plans to visit food distribution locations. Participants will be compensated up to $160 (US dollars) for completing baseline and follow-up assessments (4 assessments x $40 = $160). We will also compensate participants for using their personal smartphones for study-related use (i.e., data, texting, minutes). Participants will be compensated for up to 26 weeks, based on the number of weekly assessments completed (26 weekly assessments x $10 = $260). They will also be compensated for returning cotinine tests at 3-, 6-, and 12-months (3 tests x $30 = $90).

We will also use the following procedures to reduce attrition: 1) reminder phone calls/messages delivered via the app, SMS, or by study staff prior to scheduled assessments; 2) providing multiple ways for participants to complete assessments (i.e., in person, over the phone, online); 3) scheduling follow-up assessments at participants’ convenience; 4) obtaining names, addresses, and phone numbers of 3 collaterals (i.e., relatives, friends); and 5) utilizing Whitepages.com to search for updated contact information.

